### Usability and Quality Assurance

A usability study took place from September 2013 to January 2014 to evaluate user performance and satisfaction with the BNBD intervention. The study [70] was conducted with a prototype of the BNBD intervention, and both qualitative and quantitative data were collected. Qualitative data were analyzed using Ritterband’s eHealth model [67] to better understand how any potential barriers to intervention use (eg, level of ease of accessing the internet) could be corrected and addressed (eg, increased social presence, increased interactivity and personalization). The results of this usability study were used to revise the BNBD intervention.

Quality assurance was also undertaken to evaluate the functionality of the intervention platform in the spring of 2016. Internal reviewers, including program developers with BeHealth Solutions, LLC, and research staff at [name] LABS reviewed the intervention to identify technical problems. In addition to this, 6 parents of children aged 1 to 10 years old served as external reviewers for the program and completed 5 questionnaires to provide structured feedback on the technical operation of each session of the intervention. The goal of this step was to identify functional problems with the program (eg, broken links, incorrect routing) before conducting the RCT.

### Measures

#### Primary Outcome Measures

The primary outcome variable is sleep efficiency based on both actigraphy and parent report sleep diary data. Actigraphs are couriered to the participants and sleep diary entries are completed on the internet by the parents. Participants are asked to fill out a sleep diary for 7 consecutive days, and the child is asked to wear an actigraph during the same time period. The dates of collection of actigraphy data should correspond to the sleep diary data collection dates. Sleep diary and actigraphy data are collected at each assessment point.

##### Actigraphy

An actigraph is a battery-operated device utilizing an accelerometer to detect motor activity. We use the Philips Respironics Actiwatch 2 (Koninklijke Philips N.V., Amsterdam, NL). When an actigraph is worn, a computer chip located inside the device records movement, which is used to determine a number of sleep variables, including but not limited to sleep efficiency (captured from lights out to awakening), sleep onset, total sleep time, and night waking [9,18].

Participants are asked to have their child wear the actigraph on their child’s wrist of their less dominate hand. Children 1 to 2 years of age wear the actigraph on their ankle. Participants are instructed to record any instances in which the actigraph is removed from their child’s body for any length of time. Participants are instructed to have their child wear the actigraph for 7 days, with a minimum requirement of 5 days.

##### Sleep Diary

An internet-based sleep diary was developed based on systematic reviews by Meltzer and Mindell [24] and Wu and colleagues [71]. Sleep diaries have been validated against actigraphy and polysomnography and have demonstrated good face validity and high internal consistency when used with child participants [72]. The sleep diary requires approximately 10 min to complete. The internet-based sleep diary is housed in the Research Electronic Data Capture (REDCap) platform (Vanderbilt University, Nashville, US), a secure, electronic, data capture system [73]. The internet-based sleep diary underwent technical and usability testing by research staff and external reviewers, as well as 6 parents of children aged 1 to 10 years, to ensure the proper functionality of the measure. Parents can either complete the sleep diary directly online or print a copy and enter the information at a later point (within a 3-day time window). Data entered by participants into the internet-based sleep diary entry form are automatically populated into the REDCap database.

The sleep diary contains 25 items measuring the following variables: sleep duration, nighttime sleep duration, daytime sleep duration, sleep onset latency, bedtime, wake time, presence and frequency of night awakening, and the presence and frequency of bedtime resistance. The sleep diary also provides a measure of time spent in bed extracted from the time the light was turned off (“Down for the night”) to the time light was turned on (“Up for the day”). Sleep efficiency is calculated from these variables.

#### Secondary Outcome Measures and Measures for Exploratory Analyses

Secondary outcomes and exploratory outcomes are assessed through the administration of internet-based questionnaires to assess children’s sleep and psychosocial health, parental function, treatment barriers, and predictors to successful intervention adherence. Each participant answers 13 to 15 questionnaires based on the group assignment (intervention or usual care) and age of the child.

All measures are available in both English and French, based on whether the participant has enrolled in the English or French language trial. All secondary and exploratory outcome measures are administered on the internet via REDCap. All electronic questionnaires underwent technical and usability testing by research staff and external reviewers, as well as by 6 parents of children ages 1-10 years. All questionnaires are displayed in a sequential manner. Certain measures are age-dependent, and REDCap automatically delivers them accordingly. All measures, and the time points that each is administered, are indicated in Table 2.

Please see Multimedia Appendix 1 for a detailed description of all measures used throughout the study.

### Study Procedures

Figure 1 displays the schematic overview of the study and each step is described below.

#### Prescreening

During the prescreening process, potential participants conduct a self-screening on the BNBD website [66]. Here, interested individuals read the inclusion and exclusion criteria in lay terms and self-assess to determine if they may be eligible. If parents feel they may meet eligibility criteria and are interested in the study, they click a link directing them to the REDCap database to continue with screening. A screening information and consent form to participate in the screening process is presented, and potential participants must consent to proceed. Participants are given an opportunity to contact research staff by email to have any questions answered and concerns addressed, if they so choose.

#### Screening and Consent

After completing the screening information and consent form, participants complete the screening questionnaire to assess whether they meet inclusion criteria [63]. Participant responses to the screening questionnaire are automatically assessed in REDCap using predefined eligibility criteria, and participants immediately receive an onscreen message stating whether they are eligible or ineligible to continue. Individuals who are eligible at screening are invited to consent to participate in the full study by completing the information and consent form. The information and consent form and study data are housed in different databases. Individuals who are ineligible are informed that they do not meet the study requirements. Participants are given an opportunity to contact research staff by email to have any questions answered and concerns addressed.

#### Eligibility

After completing the information and consent form, participants complete 4 eligibility questionnaires: behavioral insomnia questionnaire [62], pediatric sleep questionnaire [64], health-related questionnaire (HRQ; author made), and single item literacy scale [65]. REDCap automatically scores these questionnaires and determines if the participant is eligible or if further review is required. Further review is required if the participant responds “yes” to any of the questions on the HRQ.

The HRQ is reviewed within 72 hours post completion by a subcommittee comprised of 3 coinvestigators including at least 1 psychologist and 1 physician (also trained in sleep medicine) to evaluate if the child has any significant physical health disorders, mental health disorders, or sleep disorders that would make them ineligible to participate.

Participants are provided with the email address of the research staff whom they may contact in the event that they have concerns or questions about the decisions related to eligibility. Participants may also request a phone call to speak with research staff about these decisions.

#### Posteligibility

Eligible participants provide their mailing address and telephone number on the identifying information questionnaire, collected in a separate REDCap database (to ensure the privacy of participants' personal information). Research staff members contact participants by telephone to confirm their mailing address and answer questions regarding study procedures. Once contact with the participant is made, the study package, including the actigraph and sleep diary, is couriered to the participant’s preferred address.

#### Baseline

Once participants receive their study package, an automated invitation email from REDCap is delivered to the participant to commence baseline measures. Participants complete 7 days of sleep diary entries and collect 7 days of actigraphy data. Participants also complete a series of questionnaires on REDCap before the end of the 7-day actigraphy and sleep diary data collection.

**Table 2 table2:** Measures and collection schedule throughout the study period. The X symbol denotes at which assessment period(s) participants complete each measure.

Measures			Screening	Eligibility	Posteligibility	Baseline	Follow-up at 4 months	Follow-up at 8 months		
**Screening measures**										
	Screening questionnaire [63]		X							
**Eligibility measures**										
	Behavioral insomnia questionnaire [62,74]			X		X^a^	X	X		
	Pediatric sleep questionnaire [64,74]			X						
	Health-related questionnaire			X						
	Single item literacy screen [65]			X						
**Posteligibility measures**										
	Identifying information questionnaire				X					
**Outcome measures**										
	Demographic questionnaire [75]					X				
	**Child sleep/insomnia**									
		Actigraphy				X	X	X		
		Sleep diary				X	X	X		
		Tayside children’s sleep questionnaire/sleep disturbance scale for children [74,76,77]				X	X	X		
	**Child daytime functioning—psychosocial/physical health**									
		Pediatric quality of life [78,79]				X	X	X		
		Child behavior checklist for ages 1½ to 5 years/child behavior checklist [80,81,82,83]				X	X	X		
		Caregiver-teacher report form/teacher report form [80,82,83]				X	X	X		
	**Parent functioning/psychosocial health**									
		Single item fatigue impact scale [84,85]				X	X	X		
		Depression, anxiety and stress scales [86-89]				X	X	X		
		Parenting scale [90,91]				X	X	X		
**Measures for exploratory analyses**										
	Children’s physical activity index [92]					X		X		
	Body mass index [93-95]					X		X		
	Parent’s rating of clinically significant improvement [96]					X	X	X		
	Treatment utilization questionnaire [97]					X	X	X		
	Willingness to pay					X	X^b^			
	Barriers to treatment participation scale [98,99]						X^b^			
	Client satisfaction questionnaire [100,101]						X^b^			
	Readiness for change [102-104]					X				
	Bedtime routines questionnaire [105]					X	X			

^a^If baseline assessment is >30 days from eligibility assessment, the behavioral insomnia questionnaire is repeated at baseline.

^b^Intervention arm only.

**Figure 1 figure1:**
[figure not shown]
Schematic overview of the study.

#### Randomization

After completion of baseline measures, participants are randomized. A blocked stratified randomization is used with 1-to-1 allocation for parents to either the intervention group or the usual care group. Participants are not blinded to their assignment group. Participants are stratified by age groups: toddler (1-2 years of age); preschool-aged (3-5 years of age); and school-aged (6-10 years of age). Blocks of 4 are used to randomize the participants for each stratum (ie, each age group).

The randomization table was created using the block random function in the R statistical software [106] and inputted into REDCap by a research staff member who is not associated with the management of participants. The only individuals who have access to the randomization table are not associated with participant management and include the research associate (EAB) who created the random allocation table based on the study design and a coinvestigator with extensive RCT design experience (RS) and the study statistician (PA), who reviewed the randomization table. The statistician conducting the primary analysis will be blinded to participant allocation to intervention or usual care groups (ie, the statistician will not be given the code for this variable).

Research staff members randomize participants using an automated REDCap procedure. The randomization table, created in Microsoft Excel, is uploaded into the REDCap database, where it cannot be modified or accessed. Only the research associate is able to view the randomization table. Once a participant completes baseline assessment, research staff members confirm all criteria are met and “trigger” the automated randomization by clicking a button within the program. An automated email is sent to participants to notify them of the randomization result.

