### Recruitment

The recruitment strategy is a multiprong approach across Canada targeting 3 groups: (1) parents, (2) external stakeholders and organizations (ie, our partners including health care provider associations), and (3) the media.

The target audience of the BNBD intervention is parents with regular access to the internet; therefore, the recruitment strategy is primarily grounded on internet-based tools, notably the study website [66] and social media, including Facebook, Twitter, Instagram, and Pinterest. However, traditional recruitment methods are also employed, including media interviews and printed posters and conference presentations, to reach both potential participants and the health care community.

We plan to enroll 500 eligible participants in this study, with 80.0% (400/500) of the sample English speaking and 20.0% (100/500) of the sample French speaking, consistent with the Canadian demographics. The study sample is also stratified on the age group of the participant’s child (toddler: 1-2 years; preschool: 3-5 years; and school-aged: 6-10 years), with equal numbers of participants enrolled from each of the 3 categories (target n=167).

Biopsychosocial model of sleep.BioOpponent process modelPhysiological arousalPsychoClassical conditioningOperant conditioningPsychological arousalEmotional regulationSocialDyadic processesFamily processesEnvironmental, cultural, socioeconomic influences

Recruitment is targeted to ensure that the study population includes representation from across Canada. Canada is divided into 4 geographical regions: Atlantic (New Brunswick, Newfoundland and Labrador, Nova Scotia, Prince Edward Island,), Central (Ontario, Quebec), Prairies and Northern Territories (Alberta, Manitoba, Saskatchewan, Northwest Territories, Nunavut, Yukon), and the West Coast (British Columbia).

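### A single fixed block size of 4 in three centrally run age strata would let staff who know it and see past allocations foresee up to one third of assignments

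*Protocol article*

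**What the plan says.** The Randomization section of the protocol article sets the scheme: "A blocked stratified randomization is used with 1-to-1 allocation for parents to either the intervention group or the usual care group". The strata are age groups only: "Participants are stratified by age groups: toddler (1-2 years of age); preschool-aged (3-5 years of age); and school-aged (6-10 years of age". The block size is a single number: "Blocks of 4 are used to randomize the participants for each stratum (ie, each age group". Under Recruitment, the three age groups are to be the same size, "with equal numbers of participants enrolled from each of the 3 categories (target n=167").

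On who knows what, the Randomization section states "Participants are not blinded to their assignment group". It names one blinded member of the trial team, the statistician who does the primary analysis. The table is loaded into REDCap, where only the research associate who made it can view it, and those with access to it take no part in managing participants. The result goes to the family by automated email.

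On who acts, once baseline is complete "research staff members confirm all criteria are met and “trigger” the automated randomization by clicking a button within the program". Before baseline, the Posteligibility section has the same category of staff speaking with families: "Research staff members contact participants by telephone to confirm their mailing address and answer questions regarding study procedures". Under Study Design, the study is coordinated through one research laboratory.

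**The concern.** Hiding the table protects the list from being read. It does not protect the sequence from being inferred. With two places per arm in every block of 4, anyone who knows the block size and has followed a stratum knows the arm of the next family as soon as one arm's two places are used. The usual mitigating feature, many sites that each see only a fragment of the sequence, is not described here: there are three strata, with one coordinating laboratory and one REDCap procedure.

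Staff also have plausible ways to learn allocations. Intervention families get the program at once while usual care families wait until after the 8-month assessment, some 4-month questionnaires go to the intervention arm only, and staff make repeated follow-up contacts.

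At stake is selection at entry. If the person who confirms criteria and triggers randomization can foresee the arm, the confirmation, or the order of families ready in the same stratum, could be influenced by it. The Data Analysis section relies on actigraphy to offset the bias of an unblinded trial. An objective outcome measure helps against biased reporting, but it cannot correct a difference in who enters each arm.

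**Working it through.** The article states no predictability figure, so there is nothing to reproduce. The inputs are all from the article: block size 4, ratio 1:1 (two places per arm in each block), three strata, and about 167 families per stratum out of 500, taken as 167, 167 and 166.

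**Share of allocations certain in advance, with block size and all earlier allocations known.** There are 6 equally likely orders of a 2+2 block.
- Positions 1 and 2: never certain.
- Position 3: certain when the first two match, probability 1/3.
- Position 4: always certain.
- Share = (0 + 0 + 1/3 + 1) / 4 = 1/3.

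**Number in this trial.** A stratum of 167 holds 41 full blocks plus 3 families: 41 × 4/3 + 1/3 = 55.0. A stratum of 166 holds 41 full blocks plus 2: 41 × 4/3 = 54.7. Total = 55.0 + 55.0 + 54.7 = 164.7, about 165 of 500 (32.9%). Simulation gives 164.7.

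**Best guess.** The chance of a correct guess at positions 1 to 4 is 1/2, 2/3, (1/3 × 1 + 2/3 × 1/2) = 2/3, and 1. The sum is 2.83 per block, and 2.83 / 4 = 70.8%, against 50% without prediction.

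**Partial knowledge.** Suppose the observer knows the block size and the block boundaries but sees each earlier allocation only with probability v. A certain prediction needs both used places of one arm to have been seen, so the share is v²/3. Incomplete last blocks lower it slightly.

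| Earlier allocations known | v²/3 | Simulated, 500 families |
|---|---|---|
| 100% | 33.3% | 32.9% |
| 75% | 18.8% | 18.5% |
| 50% | 8.3% | 8.2% |
| 25% | 2.1% | 2.1% |
| 0% | 0% | 0% |

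**Alternatives, with all earlier allocations known.**
- Known fixed block of 6: 1/4 certain, best guess 68.3%.
- Known fixed block of 8: 1/5 certain, best guess 66.6%.
- Random 4/6/8, possible sizes known but not the current one: about 2% certain (2.3% by simulation).
- Guessing the arm that is behind under random 4/6/8 (sizes equally likely) needs no knowledge of block size. Correct guesses per block are 2.83, 6 × 0.683 = 4.10 and 8 × 0.666 = 5.33. The rate is (2.83 + 4.10 + 5.33) / (4 + 6 + 8) = 12.26 / 18 = 68%.

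Varying the block size therefore removes nearly all certainty but only a little of the guessing advantage.

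**The case against.** The strongest reply is that the one-third figure needs two facts that the article does not state: that triggering staff know the block size, and that they see every earlier result in the stratum. The table's creator and reviewers are kept apart from participant management, and the result is emailed automatically to the family. What staff see on screen may be settled in a full protocol not shown here. This stands. A reader might infer that one third of allocations actually are known to staff, or that nobody except the analyst is blinded. The article says neither; it is silent on what triggering staff know.

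A reader might also infer that staff choose when to randomize. The text says only that they confirm and trigger once baseline is complete. Discretion over timing is neither described nor excluded.

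The room for selection is also narrow. REDCap scores screening and eligibility against preset criteria, flagged health questionnaires go to a subcommittee of three coinvestigators, and baseline is collected before allocation. The telephone call comes before the 7 days of recording, so a caller could not generally know which block position the family would take. That stands too. What remains is the final confirmation and the order or timing of the click.

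Printing the block size in the article adds little, since the text was written after the September 2016 launch. Finally, completion was expected in February 2018. If that date includes the 8-month assessment, few or no allocations may be left to change. That limits the prospective half of the remedy but not the retrospective check.

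**Conclusion.** The weakness is real and conditional. A fixed block of 4 in three centrally run strata, in an open trial, allows up to one third of allocations (about 165 of 500) to be foreseen with certainty and 71% to be guessed correctly. This assumes an observer who knows the block size and all earlier allocations in the stratum. The certain share falls with the square of the fraction known, to 18.5% at 75% and 8.2% at 50%.

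The documents do not show that allocation was foreseen or that selection took place, and this point should not be read as saying so. What they show is a stated design rule under which the safeguard described, restricting access to the table, does not close the route of inference, with no stated safeguard that does. With about 167 families per stratum, blocks as small as 4 are not needed for balance. The rule is worth changing because the change is nearly free, not because bias has been demonstrated.

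**What to change.** For all allocations not yet released, regenerate the list within each age stratum with block sizes varied at random, for example 4, 6 and 8, and withhold the sizes from staff who trigger randomization. State in the protocol whether those staff know the block size and whether they see earlier allocations.

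For allocations already made, compare baseline sleep efficiency (actigraphy and diary) between predictable and unpredictable block positions as a sensitivity check. Split the predictable positions by the arm that could be foreseen, since selection in opposite directions would otherwise cancel. The data are already collected. Sensitivity is modest: about 165 predictable positions give about 82 per arm, so the standard error of the arm difference is √(2/82) = 0.16 standard deviations. The check could show a large shift but would not exclude a small one.

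The cost is one run of the list generator and a re-upload to REDCap. The downside is a slightly larger possible imbalance when a stratum stops mid-block: at most 4 families with a block of 8, against 2 with a block of 4, or 12 against 6 if all three strata stopped at their worst point in the same direction. Against about 167 per stratum this is minor.
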